## Abstract

**Background:**

Knee osteoarthritis is a major cause of disability in the aging population. Based on pathological, magnetic resonance imaging (MRI) and arthroscopy studies, progressive osteoarthritis involves all tissues of the joint and includes bone marrow lesions, synovial proliferation, fat pad inflammation, and high subchondral bone turnover. Recent research suggests that abnormal perfusion in bone marrow lesions, fat pads, and subchondral bone is associated with pain in knee osteoarthritis, and that dynamic contrast-enhanced MRI is a promising method for studying micro-perfusion alteration in knee osteoarthritis. Traditional Chinese Medicine approaches have been employed for thousands of years to relieve knee osteoarthritis pain. Among herbal medicines, the Jingui external lotion is the preferred and most commonly used method in China to reduce pain in patients with knee osteoarthritis; however, there is a lack of validated evidence for its effectiveness. The purpose of this study is to explore the effectiveness of Jingui external lotion for the management of painful knee osteoarthritis in a short-term study. In addition, we will assess micro-perfusion alteration in the patellar fat pad as well as the femur and tibia subchondral bone via dynamic contrast-enhanced MRI.

**Methods/design:**

This trial is a randomized, controlled study. A total of 168 patients will be randomized into the following two groups: 1) the Jingui external lotion group (treatment group); and 2) the placebo lotion group (control group). In both groups, lotion fumigation and external washing of the patients’ knees will be administered twice a day for 14 consecutive days. Follow-up will be at regular intervals during a 4-week period with a visual analog scale to assess pain, and additional characterization with the Western Ontario and McMaster Universities Index score; rescue medication will be recorded as the extent and time pattern. In addition, micro-perfusion alteration in the patellar fat pad, femur and tibia subchondral bone will be assessed via dynamic contrast-enhanced MRI.

**Discussion:**

This study will provide clinical evidence of the efficacy of Jingui external lotion in treating knee osteoarthritis, and it will be the first randomized controlled trial to investigate micro-perfusion alteration of knee osteoarthritis with Traditional Chinese Medicine external lotion via dynamic contrast-enhanced MRI.

**Trial registration:**

ClinicalTrials.gov identifier: ChiCTR-TRC-14004727; 31 May 2014.

## Background

Knee osteoarthritis (KOA) is a major cause of disability in the aging population and a burden on healthcare resources [1,2]. The risk of disability (defined as needing help walking or climbing stairs) attributable to KOA is as great as that attributable to cardiovascular disease and greater than that due to any other medical condition in elderly persons [3]. Pathologically, osteoarthritis (OA) is characterized by progressive loss of articular cartilage and new bone formation on conventional radiography. However, it is increasingly apparent, based on pathological, magnetic resonance imaging (MRI) and arthroscopy studies, that progressive OA involves all joint tissues including bone marrow lesions, synovial proliferation, fat pad inflammation, and high subchondral bone turnover [4-7]. This progressive joint failure causes pain, physical disability, and psychological distress, although many with structural and radiological changes consistent with OA are asymptomatic [8]. In recent years, more attention has been placed on micro-perfusion alteration in KOA. Studies [9-11] employed dynamic contrast-enhanced (DCE) MRI to investigate the association between knee pain and periarticular perfusion variables. These results suggest that abnormal perfusion including bone marrow lesions, fat pad, and subchondral bone as detected by DCE MRI are associated with pain in KOA and that DCE MRI is a promising method for studying micro-perfusion alteration in KOA.

The aim of KOA treatment is to reduce pain, improve physical function, prevent disability, and enhance the quality of life over the short term. Therefore, as aging and comorbidities increase, a more convenient approach is urgently needed. In China, and increasingly worldwide, pharmacological therapy guidelines recommend topical medications as an alternative, adjunctive therapy, or even first-line therapy for KOA [12,13]. Before oral administration, topical treatments are usually recommended to relieve mild or moderate KOA pain because of their favorable safety profiles. To relieve KOA pain, herbal external therapy, including plasters, ointments, and lotions, have been used under the principle of syndrome differentiation based on Traditional Chinese Medicine (TCM) theory for thousands of years. External plasters have been reported to be very important therapies that induce muscle relaxation and invigorate blood circulation [14,15]. Jingui external lotion with fumigation and washing therapy has been employed as an effective prescription to relieve KOA pain or joint stiffness over decades, but no randomized controlled trial evidence has been published. Published Chinese literature has documented that Jingui external lotion is efficacious in treating KOA; however, these interventions have not been rigorously evaluated, and have been regarded to be less credible due to a lack of objective evidence. Therefore, we designed a randomized, single-blind, placebo-controlled trial to explore the effectiveness of Jingui external lotion for the management of painful KOA in a short-term study and the micro-perfusion alteration in the patellar fat pad, femur and tibia subchondral bone via DCE MRI.

## Methods/design

### Study design

This is a randomized, double-blind, placebo-controlled trial. The trial protocol has been approved by the Research Ethical Committee of Guangdong Provincial Hospital of TCM, (reference B2014-001-01). The trial will be conducted in accordance with the Helsinki Declaration and will be monitored by the trial agency at Guangdong Provincial Hospital of TCM.

### Recruitment and consent

KOA patients scheduled for conservative treatment at the Outpatient Department of Orthopedic Surgery, Guang Dong Provincial Hospital of TCM, will be recruited, with a target sample size of 168 subjects. All candidates will go through a standardized interview process and receive more information about the study and the treatments. Written consents will be obtained. The purpose, procedures, and potential risks and benefits of the study will also be explained thoroughly to the participants. The more painful knee will be chosen as the study knee, and if both knees have the same symptoms we will choose the right side. The participants will be able to withdraw from the study at any time without consequence. The trial will be executed from March 2014 to March 2016 including enrollment and follow-up (Figure 1).

**Figure 1 Fig1:**
[figure not shown]
**Study flow chart.** DCE MRI, dynamic contrast-enhanced magnetic resonance imaging; OA, osteoarthritis; VAS, visual analogue scale; WOMAC, Western Ontario and McMaster Universities Index.

### Inclusion criteria

Participants meeting the following criteria will be included:Meet the diagnostic criteria for KOA (American College of Rheumatology criteria [16])Aged from 50 to 80 years oldSymptomatic KOA with pain of at least 20 mm on a 100-mm visual analogue scale (VAS)Grade 0 to 3 on The Kellgren-Lawrence grading systemNo serious medical history or severe vascular lesions on lower limbsNo known drug allergies, including to the contrast agent, and no MRI contraindicationsWillingness to give written informed consent and willingness to participate in and comply with the study.

### Exclusion criteria

Participants meeting one or more of the following criteria will be excluded:MRI contraindications, or study drug allergyNon-degenerative OA, such as rheumatoid arthritis, gouty arthritis, infectious arthritis, Charcot arthritis, and so forthUnable to discontinue use of painkillersUnwilling to give informed consent.

### Interventions

Eligible patients will be randomized into the following two groups: the Jingui external lotion group (treatment group) and the placebo lotion group (control group). The enrolled patients will be administered lotions via fumigating and washing externally for 2 weeks on both knees. DCE MRI examination will be performed at baseline and 2 weeks after the intervention is completed. The participants will be given personal instructions for using the lotions by our research nurses, who will be trained before the study. Patient visits will be performed at baseline and at 1, 2, and 4 weeks after treatment. Assessments including the VAS score for pain, Western Ontario and McMaster Universities Index (WOMAC) score and complications will be made during all four visits on the study knee.

The treatment group will receive Jingui external lotion, to be used twice a day (morning and evening, approximately every 12 hours and at the same time each day) for 14 consecutive days. The Jingui external lotion will be made according to the following procedure: a mixture of TCM (composed of *Semiliquidambar cathayensis* 60 g, *Radix zanthoxyli* 60 g, *Radix aconiti kusenzoffii* 30 g, *Radix aconite* 30 g, *Tinospora sinensis merr* 30 g, *Erythrina indica lam* 30 g, *Rheum officinale* 30 g, *Cassia twig* 30 g) will be boiled in 300 ml water, reduced to 150 ml of liquid medicine, and cooled to approximately 40°C. These hot liquid medicines will be administered as Jingui external lotion to the patients’ knees.

The control group will receive placebo lotion containing a food coloring agent and a small amount of Rheum officinale that is identical to the treatment group in terms of color and odor. The manufacturing and treating procedure are the same as the treatment group.

The research nurses will be involved in the treatment procedure to ensure the correct treatment is administered and that the temperature of the lotions is tolerable to the patients. During the process, when patients experience moderate pain or VAS score over 30 mm, ibuprofen sustained-release capsules will be administrated as rescue medication. Rescue medication consumption and time will be recorded in each randomized group when used. The patients will not be allowed to use other drugs aimed at treating KOA.

### Dynamic contrast-enhanced magnetic resonance imaging examination

The subjects will receive DCE MRI on the study knee at baseline and 2 weeks after intervention using a 3.0 T scanner (Magnetom Tim Trio; Siemens Medical Solutions, Erlangen, Germany) with an eight-channel transmit-receive phased array knee coil (In vivo Corporation, Gainesville, FL, USA). The knee imaging protocol will consist of a sagittal three-dimensional high-resolution T1-weighted fast low angle shot sequence with selective water excitation (TR/TE = 500/20 ms; flip angle = 25; FOV = 18.0 cm; slice thickness = 3 mm; matrix = 320 × 240; receiver bandwidth = 200 Hz/pixel) as well as a sagittal T2-weighted fat-saturated spin echo (TR/TE = 4790/84 ms; FOV = 18.0 cm; slice thickness = 3 mm; matrix = 320 × 240; receiver bandwidth = 130 Hz/pixel). The synovial membrane will be evaluated using DCE sagittal three-dimensional T1-weighted fast low angle shot sequence with the following parameters: TR/TE = 12/3.9 ms, flip angle = 60; FOV = 15 × 15 cm, slice thickness = 5 mm, matrix = 256 × 128, receiver bandwidth = 200 Hz/pixel, temporal resolution = 30 seconds. This sequence will be acquired in contiguous 5-mm sagittal slices throughout the knee before, during and after intravenous bolus administration of double-dose contrast agent gadolinium diethylene triamine pentaacetic acid (0.2 mg/kg). Baseline pre-contrast static images as well as DCE images will be acquired after bolus injection [17,18]. The total acquisition time for the imaging protocol is 24 minutes.

Three-dimensional images of the knee joint will be rebuilt using a Leonardo workstation (Siemens Medical Solutions INC USA, [name]). The sagittal DCE sequence images and the intensity-time curve will be attained with the mean curve function. Four similar subchondral rectangular regions of interest (pixel area of 30) will be selected in the medial and lateral compartment of the distal femur and tibia plateau as well as the infra-patellar fat pad and supra-patellar fat pad. Measurement of these regions will be performed in terms of the enhanced rate and maximum upslope.

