#### Secondary outcome measure

The secondary efficacy endpoint of the study will be rescue medication, WOMAC score [20] and micro-perfusion alteration in the patellar fat pad, femur and tibia subchondral bone.

Rescue medication complicates the interpretation of trial results by having an effect on the trial outcome. It is also possible to use rescue as a trial outcome. This is common in trials of treatments for asthma, where use of β_2_-agonists for rescue therapy may be a secondary trial outcome [21]. Rescue medication in this trial is Ibuprofen, which is a short-term nonsteroidal anti-inflammatory drug. We assume that the use of rescue medication varies with time in subjects in response to worsening of their disease. Consumption and time the subjects use rescue medication will be recorded in each randomized group.

The WOMAC score is a widely used proprietary set of standardized questionnaires used by health professionals to evaluate the condition of patients with osteoarthritis of the knee and hip, including pain, stiffness, and physical functioning of the joints. The index measures five items for pain (score range 0 to 20), two for stiffness (score range 0 to 8), and 17 for physical function (score range 0 to 68). It will be measured during all the assessment visits (baseline and 1-, 2-, and 4-week follow-up).

To assess micro-perfusion alteration, two parameters will be used: 1) maximum upslope represents the initial uptake of gadolinium into the region measured by finding the fastest uptake in the first few minutes after injection; 2) an enhanced rate represents the efflux rate constant from the extravascular extracellular space to plasma, which provides an index of venous hypertension and represents the ratio of the permeability surface area product over the extravascular extracellular space. With the mean curve function, maximum upslope and enhanced rate in the distal femur and tibia plateau subchondral regions of interest, and the infra-patellar fat pad and supra-patellar fat pad regions of interest will be measured and assessed.

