## Trial status

Recruitment commenced in March 2014, and the trial is scheduled to end in March 2016.

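### The gadolinium contrast dose for the MRI is printed as 0.2 mg/kg; the unit is very probably wrong and should be verified and corrected

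*Protocol article*

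**What the plan says.** The contrast dose appears once, in the protocol article under Dynamic contrast-enhanced magnetic resonance imaging examination: "double-dose contrast agent gadolinium diethylene triamine pentaacetic acid (0.2 mg/kg"), given as an intravenous bolus. The article gives no single-dose reference, product concentration or injected volume against which a reader could check it.

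The same section sets the dynamic sequence ("TR/TE = 12/3.9 ms, flip angle = 60") and the measurement regions: "Four similar subchondral rectangular regions of interest (pixel area of 30) will be selected". It then says how the signal is obtained: "The sagittal DCE sequence images and the intensity-time curve will be attained with the mean curve function".

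Under Secondary outcome measure, micro-perfusion is summarised by maximum upslope and enhanced rate. The first is defined this way: "maximum upslope represents the initial uptake of gadolinium into the region measured by finding the fastest uptake in the first few minutes after injection". Each patient is to be scanned at baseline and again two weeks after the intervention.

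**The concern.** Milligrams per kilogram looks like the wrong unit for this agent. Gadolinium-DTPA is a heavy molecule, so 0.2 mg/kg is a tiny molar amount, which is hard to reconcile with a bolus described as a double dose.

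Two things are at stake. First, both micro-perfusion measures are read from the contrast intensity-time curve. If the injected amount barely changes the signal, that secondary endpoint measures mostly noise. Second, this is the stated dose of an injected drug, planned for 168 patients with two scans each (168 × 2 = 336 injections). Anyone reading or repeating the protocol needs a correct figure.

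**Working it through.** **Inputs from the protocol article:** dose 0.2 mg/kg; TR 12 ms; flip angle 60 degrees; regions of 30 pixels.

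**Assumed inputs, not in the article:**
- molar mass 547.6 g/mol (free acid, from its chemical formula) to 938 g/mol (dimeglumine salt)
- body weight 70 kg
- product strength 469 mg/ml
- relaxivity 3.5 to 4.5 per mM per s
- pre-contrast T1 0.3 to 1.5 s
- fraction of tissue reached by the agent 0.1 to 0.3
- distribution volume 0.2 L/kg (extracellular) or 0.04 L/kg (all in plasma)
- per-pixel signal-to-noise ratio (SNR) 20 to 100, pixels independent

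**Step 1. Convert the dose:** mmol/kg = (mg/kg) / molar mass.
- Free acid: 0.2 / 547.6 = 0.000365 mmol/kg.
- Dimeglumine salt: 0.2 / 938 = 0.000213 mmol/kg.
- Relative to 0.2 mmol/kg, this is 548 to 938 times lower.
- At 70 kg: 70 × 0.2 = 14 mg, and 14 / 469 = 0.03 ml.
- If mg meant elemental gadolinium: 0.2 / 157.25 = 0.00127 mmol/kg, still 157 times below 0.2 mmol/kg.

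**Step 2. Signal change expected from the printed sequence.** For a spoiled gradient echo, ignoring T2* effects, S = sin(a)(1 − E) / (1 − cos(a)E), where E = exp(−TR × R1), TR = 0.012 s and a = 60 degrees. Contrast raises R1 from 1/T1 to 1/T1 + relaxivity × concentration, and concentration = dose / distribution volume × tissue fraction.

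Two worked cases after extracellular distribution:
- Largest at the printed dose: 0.000365 / 0.2 × 0.3 = 0.00055 mM. With relaxivity 4.5 and T1 1.5 s, the signal rises by 0.37%.
- Smallest at 0.2 mmol/kg: 0.2 / 0.2 × 0.1 = 0.1 mM. With relaxivity 3.5 and T1 0.3 s, it rises by 9.8%.

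Full ranges:

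| Reading of the dose | After extracellular distribution | If all stayed in plasma |
|---|---|---|
| 0.2 mg/kg of the compound | 0.011% to 0.37% | 0.053% to 1.83% |
| 0.2 mg/kg as elemental gadolinium | 0.06% to 1.3% | up to 6.4% |
| 0.2 mmol/kg | 9.8% to 195% | 48% to 893% |

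**Step 3. Compare with noise.** The SD of a 30-pixel mean, relative to the signal, is 1 / (SNR × √30): 0.91% at SNR 20 and 0.18% at SNR 100. For one pre/post difference, multiply by √2: 1.29% and 0.26%.
- Printed dose, largest distributed change: 0.365 / 1.29 = 0.28 SD to 0.365 / 0.258 = 1.4 SD.
- Printed dose, all in plasma, largest: 1.83 / 1.29 = 1.4 SD to 1.83 / 0.258 = 7.1 SD.
- 0.2 mmol/kg, smallest distributed change: 9.84 / 1.29 = 7.6 SD to 9.84 / 0.258 = 38 SD.

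After distribution, the best case at the printed dose is thus well below the worst case at 0.2 mmol/kg.

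**The case against.** The strongest objection is that the article contains no second dose figure for the printed one to contradict. Calling 0.2 mg/kg too low for a double dose needs a single dose from outside, and the comparator of 0.2 mmol/kg appears nowhere in the text. This stands as far as the intended unit goes: mmol/kg is an inference. It does not rescue the printed figure. The molar conversion needs only the chemistry of the named compound, and the signal calculation uses the article's own sequence with openly assumed ranges rather than a remembered label dose.

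The signal model can also be criticised. Its plasma case reaches about 7 SD at the higher SNR, and the elemental-gadolinium reading reaches 6.4%, about 25 SD (6.4 / 0.258). A dynamic series offers more frames than one pre/post pair, so noise could be averaged down. The plasma case assumes full mixing, so it is not a strict limit on first-pass enhancement. These points are fair. They are why the claim is little or no measurable enhancement, not none, and why the percentages show order of magnitude only. They do not make 0.2 mg/kg a plausible dose.

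Finally, radiology staff would ordinarily work from a product label, and a volume of about 0.03 ml would hardly pass unnoticed. The likely practical effect is therefore a misprint. That limits the weight of the point. But this is a figure stated wrongly, not a detail left to a fuller document, so condensation into an article does not excuse it.

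**Conclusion.** The point holds: the dose is very probably wrong as written. Every mg/kg reading examined falls 157 to 938 times below 0.2 mmol/kg. The size of the shortfall rests on molar mass and on 0.2 mmol/kg as the comparator; the expected signal changes rest on the assumed relaxivity, T1, tissue fraction, distribution volume and noise.

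The consequence is confined to the micro-perfusion secondary outcome and to the accuracy of a stated drug dose. The primary VAS comparison, the sample size and the other secondary outcomes are not touched. There is no evidence that any patient received the printed dose. Confidence is high that the figure needs correcting, and lower about which unit was intended.

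**What to change.** Check the dose against the imaging manual and the product label, then correct the figure and unit in the MRI examination section. If mmol/kg proves to be right, only the unit changes.

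The Trial status section says "Recruitment commenced in March 2014, and the trial is scheduled to end in March 2016", so scans may already have been done. Check the existing contrast records to confirm the dose actually given. The cost is a one-line correction and a records check, with no extra patients, scans or analyses.

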### Outcome measures

#### Primary outcome measure

The primary efficacy endpoint of the study will be VAS, which is a pain score ranging from 0 mm (no pain) to 100 mm (worst pain ever experienced) [19], measured during all the assessment visits (baseline and 1-, 2-, and 4-week follow-up). The VAS score is usually a horizontal line, 100 mm in length, anchored by word descriptors at each end. Patients mark the point of their current pain on the line. The VAS score is then determined by measuring in millimeters from the left end of the line to the point that the patient marked.

#### Secondary outcome measure

The secondary efficacy endpoint of the study will be rescue medication, WOMAC score [20] and micro-perfusion alteration in the patellar fat pad, femur and tibia subchondral bone.

Rescue medication complicates the interpretation of trial results by having an effect on the trial outcome. It is also possible to use rescue as a trial outcome. This is common in trials of treatments for asthma, where use of β_2_-agonists for rescue therapy may be a secondary trial outcome [21]. Rescue medication in this trial is Ibuprofen, which is a short-term nonsteroidal anti-inflammatory drug. We assume that the use of rescue medication varies with time in subjects in response to worsening of their disease. Consumption and time the subjects use rescue medication will be recorded in each randomized group.

The WOMAC score is a widely used proprietary set of standardized questionnaires used by health professionals to evaluate the condition of patients with osteoarthritis of the knee and hip, including pain, stiffness, and physical functioning of the joints. The index measures five items for pain (score range 0 to 20), two for stiffness (score range 0 to 8), and 17 for physical function (score range 0 to 68). It will be measured during all the assessment visits (baseline and 1-, 2-, and 4-week follow-up).

To assess micro-perfusion alteration, two parameters will be used: 1) maximum upslope represents the initial uptake of gadolinium into the region measured by finding the fastest uptake in the first few minutes after injection; 2) an enhanced rate represents the efflux rate constant from the extravascular extracellular space to plasma, which provides an index of venous hypertension and represents the ratio of the permeability surface area product over the extravascular extracellular space. With the mean curve function, maximum upslope and enhanced rate in the distal femur and tibia plateau subchondral regions of interest, and the infra-patellar fat pad and supra-patellar fat pad regions of interest will be measured and assessed.

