## Discussion

This study will provide clinical evidence on the efficacy of Jingui external lotion in treating KOA, and it will be the first randomized controlled trial to investigate micro-perfusion alteration of KOA with TCM external lotion using a DCE MRI technique. In TCM, KOA development is attributed to deficiency of the liver and kidney, and deficiency of qi and blood, attack of wind-cold-dampness evils, obstruction of channels and collaterals, qi and blood stagnation [24]. Thus, TCM that can promote blood circulation, remove blood stasis, and activate meridians to stop pain may be effective for KOA [13]. Fumigation and washing of TCM has recently been considered an inexpensive and convenient therapeutic approach for KOA [25]. Jingui external lotion is a classical and well-known external therapy in the orthopedic departments of TCM and has been demonstrated to provide a satisfactory effect for KOA in the clinic. Well-designed randomized controlled trials are needed to examine the efficacy of TCM treatments for OA.

It has been revealed that Chinese medicine promoting circulation and removing stasis could reduce intraosseous pressure [26]. Intraosseous hypertension has been reported to have an association with deep pain in patients with KOA [27]. To date, there is a lack of evidence to support the hypothesis that Chinese medicine promotes circulation; therefore, we will employ a DCE MRI technique to study micro-perfusion alteration, with the aim of attaining objective evidence of Jingui external lotion effectiveness in the treatment of patients with KOA.

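### The enhanced rate is labelled an efflux constant and venous-hypertension index, but the only method described is reading an intensity-time curve

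*Protocol article*

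**What the plan says.** The protocol article lists micro-perfusion alteration as a secondary endpoint and gives it two parameters (Secondary outcome measure).

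- The first is descriptive: "maximum upslope represents the initial uptake of gadolinium into the region measured by finding the fastest uptake in the first few minutes after injection".
- The second is given a physiological meaning: "an enhanced rate represents the efflux rate constant from the extravascular extracellular space to plasma, which provides an index of venous hypertension". The same sentence adds that it "represents the ratio of the permeability surface area product over the extravascular extracellular space".

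The method appears in two places. The section on the dynamic contrast-enhanced MRI examination says: "The sagittal DCE sequence images and the intensity-time curve will be attained with the mean curve function". The Secondary outcome measure section assigns both parameters to that same tool: "With the mean curve function, maximum upslope and enhanced rate in the distal femur and tibia plateau subchondral regions of interest" and in the two fat pad regions. The dynamic sequence has "TR/TE = 12/3.9 ms, flip angle = 60" and "temporal resolution = 30 seconds".

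The article names no compartment model, input function, baseline T1 map or conversion from signal to concentration, and it gives no formula for the enhanced rate. The Discussion says the imaging is done "with the aim of attaining objective evidence of Jingui external lotion effectiveness in the treatment of patients with KOA".

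**The concern.** An efflux rate constant, and a ratio of permeability surface area product to extravascular extracellular space, are parameters of a kinetic model. They come from fitting that model to a curve; they are not features one reads off it. Maximum upslope can be read off directly. The article treats the two parameters as the same kind of read-out, so for the enhanced rate the stated meaning and the stated method do not match.

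This goes beyond an omitted detail. The article states what the number means and how it is obtained, and the second does not deliver the first. If the text is followed literally, a difference in signal enhancement between the groups would carry the label of a difference in efflux or venous hypertension, neither of which the described step measures.

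**Working it through.** The plan gives no figure for this parameter, so there is nothing to reproduce. Two checks apply.

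**Check 1: meaning against method**

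| Parameter | Stated meaning | Stated method | Match |
|---|---|---|---|
| Maximum upslope | Fastest early uptake | Mean curve function | Yes, a feature of the curve |
| Enhanced rate | Efflux constant; permeability surface area product / extravascular space; venous-hypertension index | Mean curve function | Not without a fitted model, and none is named |

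Scope: 4 subchondral regions + 2 fat pads = 6 regions; 6 × 2 parameters = 12 read-outs, of which 6 are enhanced rate. This counts what is touched. It is not an effect size.

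**Check 2: does a descriptive curve value follow the efflux constant?**

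*From the article:* TR 12 ms, flip angle 60, one frame per 30 s.

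*Assumed, not from the article:* tissue values, relaxivity 4.0, a 10-minute window, no echo-time decay, no noise, and a plasma curve Cp(t) = 0.2 × [3.99 exp(−0.144t) + 4.78 exp(−0.0111t)], t in minutes. The scale factor only sets the size of the illustration and says nothing about the trial's contrast dose.

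*Formulas:*
- Efflux constant: kep = Ktrans/ve (transfer constant over extravascular extracellular fraction).
- Tissue concentration: Ct(t) = Ktrans ∫ Cp(u) exp(−kep(t−u)) du.
- Signal: S = sin α (1−E)/(1−E cos α), with E = exp(−TR(1/T10 + 4.0 Ct)).
- Relative enhancement: S/S0 − 1.
- Signal-based two-compartment (Brix-type) fit to the same curve: A·kep/(kep−kel)·[exp(−kel t) − exp(−kep t)]. The two rates are interchangeable in this formula; the faster is taken as kep.

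| Ktrans (/min) | ve | T10 (s) | True kep (/min) | Peak relative enhancement | Peak/time-to-peak (/min) | Fitted kep (/min) |
|---|---|---|---|---|---|---|
| 0.02 | 0.10 | 0.6 | 0.20 | 0.25 | 0.026 | 0.253 |
| 0.04 | 0.20 | 0.6 | 0.20 | 0.49 | 0.051 | 0.257 |
| 0.08 | 0.40 | 0.6 | 0.20 | 0.96 | 0.101 | 0.266 |
| 0.02 | 0.10 | 0.4 | 0.20 | 0.16 | 0.017 | 0.253 |
| 0.02 | 0.10 | 0.9 | 0.20 | 0.37 | 0.039 | 0.253 |
| 0.02 | 0.05 | 0.6 | 0.40 | 0.14 | 0.024 | 0.451 |
| 0.04 | 0.10 | 0.6 | 0.40 | 0.29 | 0.048 | 0.453 |
| 0.02 | 0.20 | 0.6 | 0.10 | 0.37 | 0.038 | 0.168 |

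*Results:*
1. With kep fixed at 0.20/min (first five rows), peak enhancement varies 0.96/0.16 = 6-fold.
2. Starting from the first row, doubling kep by halving ve lowers the peak from 0.25 to 0.14, while peak/time-to-peak hardly moves (0.026 to 0.024). Doubling kep by doubling Ktrans raises the peak from 0.25 to 0.29. The same change in efflux can therefore push the read-out either way.
3. In the rows with kep of 0.20 or 0.10 the peak is the last sample (9.5 min). A longer window could only raise those peaks, so it would not remove the fall in result 2.
4. The fitted constant follows the true one with upward bias: 0.168 for 0.10, 0.253 to 0.266 for 0.20, and about 0.45 for 0.40.

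**The case against.** The strongest reply is that this is a condensed article. A region-of-interest intensity-time curve is also the input to a compartment fit, and the text names no model but excludes none. The full protocol may specify one, and result 4 shows that such a fit could approximate the defined constant without an input function or T1 map. This stands. It rules out saying that no model will be fitted, or that the planned scans cannot yield an efflux constant. It does not remove the mismatch, because the article does say how the parameter is obtained and that step alone does not produce it.

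Other stronger readings are tempting but unsupported:

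- **A venous-hypertension conclusion.** A reader might infer that the article promises to show venous hypertension falling. It does not. The Discussion mentions intraosseous hypertension as background, and its perfusion aim also rests on maximum upslope.
- **No direction of benefit, hence an irrefutable claim.** A reader might argue that inflammation would raise the constant and poor venous outflow would lower it. The article states neither effect, so the argument needs outside physiology. Two-sided testing is ordinary practice.
- **Scanner gain as a further confounder.** A constant gain cancels in a relative measure.
- **Efficacy resting on perfusion.** VAS is already the primary efficacy endpoint and perfusion is secondary.

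**Conclusion.** The point holds for one parameter as described. The enhanced rate carries a model-based label that its only stated method does not deliver, so a group difference in it could not be read as a change in efflux or venous hypertension. A descriptive value from the curve can vary several-fold at constant efflux and can move against it.

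The sizes in the table rest on assumed tissue values and a noise-free signal. They illustrate the possible discrepancy and do not predict it for this trial. The qualitative result needs less: a descriptive enhancement value also depends on transfer, distribution volume and native T1.

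The reach is limited to half of the perfusion read-outs within one secondary endpoint. Maximum upslope, VAS, WOMAC, the sample size and alpha do not change. It is still worth correcting, because the correction is cheap and determines what the perfusion result may be said to show.

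**What to change.** In the Secondary outcome measure section, do one of the following:

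1. **Describe what the curve delivers.** Define the enhanced rate as relative enhancement, for example (peak signal − pre-contrast signal)/pre-contrast signal, and delete the efflux-constant and venous-hypertension interpretation.
2. **Keep the interpretation and measure it.** Obtain the parameter by fitting a named compartment model to the curves already acquired, and state which fitted rate is reported as the efflux constant. The upward bias in the illustration suggests treating a simple signal-based fit as approximate.

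The first option costs wording and a more modest mechanistic claim. The second costs off-line curve fitting. Neither needs extra scans or patients.
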